Since the study protocol was first authorised for this trial in 2015, a wealth of studies has been published on TXA use in THA and TKA further advocating its use. However, determination of the most effective duration of TXA treatment, dosage and regimen for major joint arthroplasty has barely been investigated. Most studies focus on the intra-operative period [18, 19] with little published work into treatment regimes that extend beyond a dose 3 h post-operatively. However, we postulate that the period of greatest importance is the first 24 post-operative hours. This theory is based upon an internal audit carried out at Musgrave Park Hospital, Belfast, Northern Ireland, on 361 consecutive patients undergoing THA. We compared patients’ intra-operative blood loss to their total blood loss at 2 days post-operatively. Total blood loss was calculated indirectly using equations based on a change in haematocrit [20, 21]. The average directly measured intra-operative blood loss was 223 mL (range 50–1204 mL) and the average indirectly calculated total blood loss was 1377 mL (range 263–3864 mL). On average, the total loss was over six times the measured loss in theatre. Other relevant findings from this audit were that on average 90% of total loss occurs in the first 24 post-operative hours and that intra-operative blood loss grossly underestimates total blood loss, thus making it a poor predictor of total loss. Based on this audit and other literature demonstrating that blood loss continues in the first 24 h post-operatively [22–26], we hypothesise that using TXA up to 24 h post-operatively has the potential to reduce blood loss further following THA and TKA, compared to a single peri-operative dose of TXA. Since there is evidence that oral administration is equally efficacious as intravenous administration [27, 28], this study uses oral TXA post-operatively as a cheaper and less labour-intensive mode of delivery than either IV bolus or infusion regimes.

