### Statistical and interim analysis

Based on a mean (standard deviation) of 1225 (499) mL of blood loss and a clinically significant difference of 150 mL (12%) between the two TXA groups, originally the trial required 233 participants per group at 90% power and 0.05 level of significance. Due to the proven greater blood loss in control group 3, there were only half this number of participants in this group (*n* = 117). This would result in a total of 1166 participants (583 TKA and 583 THA), as a negligible dropout rate was expected. The clinically significant difference of 150 mL was based on an internal audit of blood loss in primary THA and TKA patients. The audit found that the average calculated blood loss was almost 1500 mL. Based on this and the clinical opinion of the anaesthetists, surgeons, and haematologist involved in the study, a value of 150 mL (10% of the average blood loss) was considered to be clinically significant.

Based on the strong rationale that TXA is effective at reducing blood loss for THA and TKA, a planned interim analysis was performed to compare the control and combined intervention groups to determine whether recruitment to control group 3 should continue. A power calculation determined that a sample size of 98 patients would be required to detect a clinically relevant difference of 450 mL of blood loss between the control and combined intervention groups at the significance level of *p* = 0.01 and 90% power. The analysis was performed separately for THA and TKA participants and also for the combined participants.

Following this interim analysis, the DMEC recommended to the TSC that randomisation to control group 3 of patients recruited should be stopped. A minimum of 932 patients is required with an allocation of 466 (233 TKA and 233 THA) to intervention group 1 and 466 (233 TKA and 233 THA) to intervention group 2. Atogether, 134 patients were randomised to control group 3. Eligible participants are now allocated to intervention group 1 or intervention group 2 with an allocation ratio of 1:1.

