Analyses will be on an intention-to-treat basis and at an a priori significance level of *p* = 0.05. Baseline characteristics and outcome measures will be summarised as mean and standard deviation, median and inter-quartile range or numbers and proportions (%) depending on the scale of measurement. For the primary outcome and other continuous outcomes, analysis of variance with contrasts will be used to compare both intervention groups and also the intervention groups combined versus the control group. Analysis of covariance will be used to adjust for baseline and other covariates where appropriate. The chi-squared test will be used to test the difference in the proportions between the groups for the categorical variables. All analyses will be performed for THA and TKA separately and also combined. Subgroup analyses will be performed on the primary outcome measure for THA/TKA, creatinine, age, gender and body mass index. A statistical analysis plan will be written and approved prior to commencement of any analyses.

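### If the small no-TXA arm varies more than the TXA arms, the pooled-variance ANOVA contrasts make the control interval too narrow and the primary interval slightly too wide (minor)

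*Protocol article*

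**What the plan says.** Under Statistical and interim analysis, the protocol article fixes the model for blood loss and the remaining continuous measures in these terms: "analysis of variance with contrasts will be used to compare both intervention groups and also the intervention groups combined versus the control group". Covariates enter the same way: "Analysis of covariance will be used to adjust for baseline and other covariates where appropriate". The analysis sets are also fixed: "All analyses will be performed for THA and TKA separately and also combined". The significance level is 0.05. Nothing is said about equal variances, separate-variance tests, robust errors or transformation. The section ends: "A statistical analysis plan will be written and approved prior to commencement of any analyses".

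The same section gives a single mean and SD, 1225 (499) mL, not split by arm. It explains the smaller control arm by its expected mean: "Due to the proven greater blood loss in control group 3, there were only half this number of participants in this group". The interim calculation was sized for "a clinically relevant difference of 450 mL of blood loss between the control and combined intervention groups". After randomisation to group 3 was stopped, the minimum sizes are 466 and 466 for groups 1 and 2 (233 per joint each), with 134 patients randomised to control.

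Under Objectives, group 1 versus group 2 is the primary question. Comparison with no TXA belongs to the secondary objective.

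**The concern.** A contrast from an ordinary three-group ANOVA takes its standard error from one residual variance, weighted by group size. Groups 1 and 2 supply 932 of the 1066 patients, so they dominate that variance. If the control arm has the larger spread, two things follow. The uncertainty of the control mean, which is the main source of error in the control contrast, is understated. Part of the control arm's extra spread is also carried into the comparison of groups 1 and 2, to which the control arm does not belong.

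A larger control spread is plausible. Blood loss is non-negative, and the internal audit described in the Background has a mean of 1377 mL and a range of 263 to 3864 mL: 1114 mL below the mean but 2487 mL above it. The outcome formula multiplies blood volume by the fall in haematocrit and divides by average haematocrit, so spread tends to grow with the amount lost. The control arm is the one expected to lose most.

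At stake are the coverage of the TXA versus no-TXA interval, to be produced for hips, knees and both combined, and a little of the per-joint power of the primary comparison.

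**Working it through.** **The plan's own figure.** Two-sided 0.05, 90% power, difference 150 mL, SD 499 mL:
n = 2 × (1.960 + 1.282)² × 499² / 150² = 232.6, so 233 per group. The stated figure reproduces, and 2 × (233 + 233 + 117) = 1166.

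**Inputs.** From the article: TXA SD 499 mL; n = 466/466/134 combined and 233/233 per joint; alpha 0.05. Assumed: 67 controls per joint (even split of 134), and a control SD of r × 499. The documents do not give r, so a range is used:
- constant coefficient of variation at the audit means: 1377/1225 = 1.12, and 1500/1225 = 1.22 (the article says almost 1500 mL);
- constant coefficient of variation at 1225 + 450 mL: 1675/1225 = 1.37, a control SD of about 682 mL.

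**Formulas.**
- Pooled variance: MSE = [465 × 499² + 465 × 499² + 133 × (499r)²] / 1063
- Control contrast, pooled SE: √[MSE × (1/932 + 1/134)]
- Control contrast, true SE: √[499²/932 + (499r)²/134]
- Non-coverage of the nominal 95% interval: 2 × [1 − Φ(1.96 × pooled SE / true SE)]
- Group 1 versus 2: pooled SE / true SE = √MSE / 499. Per-joint power uses 150 / (499 × √(2/233)) = 3.245 and equals Φ(3.245 − 1.96 × that ratio).

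**Worked case, r = 1.37, combined.** √MSE = 525.4 mL. Pooled SE = 48.5 mL and true SE = 61.2 mL, a ratio of 0.79. Non-coverage = 2 × [1 − Φ(1.556)] = 12.0%. The 95% half-width is 1.96 × 48.5 = 95 mL where it should be 1.96 × 61.2 = 120 mL.

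**Results.**

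| r | Control contrast: pooled/true SE | Control interval non-coverage | Group 1 v 2: pooled/true SE | Group 1 v 2 power per joint | Group 1 v 2 power, combined |
|---|---|---|---|---|---|
| 0.8 | 1.18 | 2.1% | 0.98 | 90.8% | 99.6% |
| 1.0 | 1.00 | 5.0% | 1.00 | 90.1% | 99.6% |
| 1.1 | 0.93 | 6.8% | 1.01 | 89.6% | 99.5% |
| 1.12 | 0.92 | 7.2% | 1.02 | 89.5% | 99.5% |
| 1.22 | 0.86 | 9.2% | 1.03 | 89.0% | 99.5% |
| 1.37 | 0.79 | 12.0% | 1.05 | 88.1% | 99.4% |
| 1.5 | 0.74 | 14.5% | 1.08 | 87.2% | 99.3% |

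The control-contrast columns are the same per joint to within rounding, because the proportions are the same. Type I error of the group 1 versus 2 contrast falls below nominal, to 4.7% at r = 1.1 and 3.9% at r = 1.37.

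**Check by simulation** (normal data, 40,000 trials per setting). At r = 1.37 the pooled control contrast rejected a true null in 11.8% to 11.9% of trials, and per-joint primary power was 87.8%. Over r = 1 to 1.5, a separate-variance control contrast held 4.7% to 5.1%, and a group 1 versus 2 test using only those groups kept 89.7% to 89.9% per-joint power.

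**Does the conclusion change?** At r = 1.37 a true 450 mL control difference is 450/61.2 = 7.4 true SEs from zero combined and 450/86.5 = 5.2 per joint. It would be significant under either method.

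**The case against.** The strongest objection is that the premise is not in the documents. The article gives one SD, and its remark on greater control blood loss concerns the mean. An asymmetric audit range shows skew within one set of hip patients; it does not show that spread rises with the mean across arms. This stands, and it is why every result above is conditional on r.

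Second, 450 mL is a difference to be detected, not a forecast. This also stands. The ratio of 1.37 is therefore the upper end of the range; the audit means point to about 1.12 to 1.22, with non-coverage of about 7% to 9%. For the same reason the percentages should be read as interval non-coverage and not as a false-positive rate: a ratio derived from a mean difference cannot be combined with equal means.

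Third, variance checks and robust errors are often settled in a statistical analysis plan, which is announced but not shown. That plan may already deal with this. The article nevertheless commits to a named method for named contrasts, and a plan that follows it with usual defaults inherits the pooled error.

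Two stronger readings are tempting. One is that the intervals are wrong as planned. The documents do not support that, because at r = 1 there is no distortion and below 1 both directions reverse. The other is that the primary comparison or the TXA versus no-TXA conclusion is unsafe. The primary effect is small and conservative, and a control difference near 450 mL would survive. The decision to close group 3 came from the interim analysis, not from this final contrast.

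**Conclusion.** The point holds in conditional form and is minor. If the control arm's SD exceeds that of the TXA arms by 10% to 37%, pooled contrasts give a control-contrast SE about 7% to 21% too small, so the nominal 95% interval covers about 93% down to 88% of the time. The primary contrast's SE is then about 1% to 5% too large, costing at most about 2 points of per-joint power and almost nothing in the combined analysis. The harm is an overconfident interval on a secondary comparison, not a reversed conclusion.

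This rests on the assumed SD ratio, equal SDs of 499 mL in groups 1 and 2, an even split of the 134 controls by joint, and approximately normal sample means. The direction depends wholly on the control arm being the more variable one, which is plausible but not documented.

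**What to change.** In the analysis plan, for blood loss and the other continuous outcomes:
- estimate group 1 versus group 2 from those two groups only, so that the residual variance comes from the arms being compared;
- use a Welch-type contrast or heteroscedasticity-robust standard errors for any comparison involving group 3;
- apply the same rule in the analysis of covariance, and in the hip, knee and combined analyses.

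The cost is a sentence of wording and a software option; no further patients or data are needed. The downside is a wider control-contrast interval: hardly any wider if the variances prove equal, about 7% wider at r = 1.1 (50.2/46.7) and about 26% at r = 1.37 (61.2/48.5). In the last two cases the extra width is uncertainty that the pooled interval leaves out.

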### Recruitment and consent

TRAC-24 originally required a minimum of 1166 patients to be recruited. Recruitment would stop when 583 participants were recruited for both TKA and THA. However, following a DMEC recommendation, recruitment to control group 3 was stopped, after approval from the sponsor, the regional ethics committee and the Medicines and Healthcare Products Regulatory Agency (MHRA) was acquired. At this point, 672 participants had been recruited to the study. This meant that a minimum of 466 THA and 466 TKA were now required to complete the study with a minimum overall recruitment of 1066, recruiting only to groups 1 and 2. Potentially eligible patients are identified and screened by members of the clinical study team based on the inclusion and exclusion criteria outlined above.

A cover letter and a patient information sheet approved by the Research Ethics Committee is sent to potential patients informing them about the study. The latter contains a contact number should they have any questions or wish to discuss the study further. The study is then discussed directly with the patient at a pre-operative clinic (approximately 7 to 10 days prior to operation) or following admission for surgery. Informed consent is taken by a member of the research team after the participant has been given the opportunity to ask further questions and agrees to participate.

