### Randomisation and blinding procedures

At the outset of the trial, eligible participants were allocated to intervention group 1, intervention group 2 or control group 3 (standard care) with an allocation ratio of 2:2:1. After the DMEC recommended stopping randomisation to control group 3, eligible participants were then allocated to intervention group 1 or intervention group 2 with an allocation ratio of 1:1. Blocked randomisation with randomly permuted block sizes is used. Participants are stratified according to operation type, surgeon and creatinine level, resulting in 16 possible stratifications (Fig. 3):

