Originally, this study had been designed with three arms to include both interventions and also a control arm, which was standard care without TXA. The numbers allocated to each arm were in the ratio 2:2:1. It was felt necessary to include the no TXA arm, control group 3, because although TXA is known to reduce blood loss, it was not the standard of care in our unit. However, it was stipulated in the protocol that there must be an interim analysis once 100 THA and 100 TKA patients had been recruited to decide on the continuation of the control group 3. At that time, 40 patients had been recruited into this group. Following this analysis, the DMEC recommended dropping control group 3, which was ratified by the TSC. This change was implemented following approvals from the sponsor, the research ethics committee and MHRA. This also resulted in a change in practice in our unit, with TXA being considered for all primary joint patients at the discretion of the anaesthetist.

The authors are aware of some limitations to this study. Firstly, it is a single-centre study; therefore, it could be argued that the results are not transferable to other centres due to different clinical practices. Secondly, randomisation is performed using sealed envelopes with tamper-proof labels instead of an automated system. While both systems were considered during the study design, it was decided that as it was a single-centre study with robust checks by the study site and by the NICTU, sealed envelopes were sufficient.

With TRAC-24, we intend to determine if the effect of TXA can be potentiated by continuing its administration post-operatively, at the time of greatest loss.

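### As written, the secondary comparison of TXA with no TXA sets the control group partly against participants recruited after that group had closed

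*Protocol article*

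**What the plan says.** All references are to the Protocol article.

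- **The contrast.** Statistical and interim analysis specifies, for the primary and other continuous outcomes, analysis of variance with contrasts "to compare both intervention groups and also the intervention groups combined versus the control group".
- **The analysis set and adjustment.** The same section states "Analyses will be on an intention-to-treat basis and at an a priori significance level of" 0.05, and adds: "Analysis of covariance will be used to adjust for baseline and other covariates where appropriate". It names neither calendar period nor allocation phase as a covariate. Categorical variables get a chi-squared test.
- **Closure of group 3.** Recruitment and consent says of the moment when recruitment to group 3 stopped: "At this point, 672 participants had been recruited to the study". Statistical and interim analysis adds that "134 patients were randomised to control group 3".
- **Allocation afterwards.** Randomisation and blinding procedures says that "eligible participants were then allocated to intervention group 1 or intervention group 2 with an allocation ratio of 1:1". Recruitment and consent sets the new target "with a minimum overall recruitment of 1066, recruiting only to groups 1 and 2".
- **Role of the no-TXA comparison.** Under Objectives, the primary question is group 1 against group 2. Comparison with no TXA belongs to the secondary objective.

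**The concern.** The analysis paragraph was published after group 3 had closed, in an article that describes the closure and the new ratio. Its control contrast nevertheless reads as it would for a trial that kept three groups open throughout. Followed literally, every TXA participant enters the comparison with control, including those who could never have been allocated to control.

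Randomisation protects a comparison only between people who could have received either allocation. For later TXA participants against earlier controls, a difference in outcome mixes the effect of TXA with anything that changed between the phases: case mix, peri-operative care or the way outcomes are collected. Stratification by operation type, surgeon and creatinine balances TXA and control only among those randomised while all three groups were open.

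At stake are the size of the TXA versus no-TXA effect on blood loss and, if the same data sets are used there, the comparisons with control for transfusion, 90-day events and costs.

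**Working it through.** **1. The article's own figures.** Inputs from Statistical and interim analysis: SD 499 mL, difference 150 mL, 90% power, significance level 0.05 (two-sided assumed).

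- n per group = 2 × [499 × (1.960 + 1.282) / 150]² ≈ 232.6, rounded up to 233. This agrees with the article.
- Original total: 2 × (233 + 233 + 117) = 1166. Revised minimum: 932 + 134 = 1066. Both agree.
- Controls expected at 672 recruited under 2:2:1: 672 / 5 = 134.4, against 134 reported.

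**2. Concurrent and non-concurrent TXA participants.**

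- TXA participants at closure: 672 − 134 = 538.
- Still to be recruited to the planned minimum: 932 − 538 = 394; equally 1066 − 672 = 394.
- Share of the TXA side: 394 / 932 = 42.3%.
- Trial status reports 879 recruited at the end of February 2018, so 879 − 672 = 207 of these later participants were already in the trial.

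**3. How drift enters the contrast.** Suppose mean loss under TXA is m in the first phase and m + d in the second. The pooled TXA mean is (538m + 394(m + d)) / 932 = m + 0.423d. Controls exist only in the first phase, so the contrast is shifted by 0.423d. The article gives no value for d; those below are assumptions.

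The standard error with all TXA participants, taking SD 499 in every group, is 499 × √(1/134 + 1/932) = 46.1 mL. The last column is the two-sided rejection rate when TXA truly has no effect, at nominal 5%.

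| Assumed drift d (mL) | Bias (mL) | Rejection rate |
|---|---|---|
| 25 | 10.6 | 5.6% |
| 50 | 21.1 | 7.4% |
| 100 | 42.3 | 15.0% |
| 150 | 63.4 | 28.0% |

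The interim calculation treated 450 mL as the relevant difference from control. Against that, 21.1 / 450 = 4.7% and 63.4 / 450 = 14.1%.

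**4. Cost of using concurrent participants only.**

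- SE = 499 × √(1/134 + 1/538) = 48.2 mL. Ratio to the pooled SE: 48.18 / 46.10 = 1.045.
- Power for 450 mL is above 99.9% either way. It is also above 99.9% for each joint separately, with about 67 versus 269 (an even split between joints is assumed).
- Power for 150 mL goes from 90.2% to 87.6%.

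**5. Group 1 versus group 2.** The ratio between these groups is 2:2 before closure and 1:1 after it. Each contributes the same share of early and late participants, so a drift common to both cancels from their difference.

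**The case against.** The strongest reply is that the pooling is inferred. The article never says in words that all 932 TXA participants enter the control contrast, its covariance clause leaves room for a phase term, and it promises a statistical analysis plan before any analysis. That plan may already deal with the point. This stands as a limit on certainty. It does not remove the point, because the article commits to a specific contrast, after the design changed, that no longer matches the randomisation. The covariance clause also cannot help the categorical outcomes, since a chi-squared test has no place for a phase term.

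Several stronger readings are tempting, and the article does not support them:

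- **That the primary result is at risk.** It is not biased, for the reason in step 5 of the working.
- **That the article documents drift.** The Discussion dates the fall in operations from when the study was planned, not from closure, and the winter effect is seasonal. The move to electronic records for 90-day data also covers earlier participants whose data could not otherwise be obtained, which reduces differential ascertainment though it may not remove it; it cannot affect a 48 h outcome. On unit practice the Discussion says "This also resulted in a change in practice in our unit, with TXA being considered for all primary joint patients", but groups 1 and 2 already receive TXA by allocation. The article shows that drift is possible, not that it occurred.
- **That the quoted contrast governs every outcome.** It covers continuous outcomes. Categorical outcomes and costs have their own stated methods. Non-concurrency would affect those comparisons with control too, but the quoted sentence does not specify them.
- **That controls in a common error term harm the group 1 versus group 2 test.** A shared error term is ordinary in analysis of variance. The article gives no separate control SD from which to show a loss.

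**Conclusion.** The point holds as a secondary-analysis issue. Read as written, the control contrast is partly non-concurrent: 538 of the planned 932 TXA participants were randomised alongside the 134 controls, and at least 394 (42%) were not. These counts follow directly from the article. The effect on the estimate is 0.42 times whatever drift occurred, in either direction; the 21 to 63 mL range rests entirely on an assumed drift of 50 to 150 mL.

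Bias of that size would not overturn a difference near 450 mL. It could distort the reported size of the effect. It would matter more where the true difference from control is small, as the rejection rates under no effect show. The conclusion assumes that the unrestricted intention-to-treat contrast means all randomised participants, and that the unseen analysis plan does not already restrict it.

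**What to change.** Before any analysis, state the following in the protocol or the statistical analysis plan:

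1. The main control contrast uses only participants randomised while group 3 was open (134 versus about 538), adjusted for operation type, surgeon and creatinine level. This remains intention-to-treat, because the restriction depends on when a participant was randomised and not on treatment received.
2. The same restriction applies to the categorical, safety and cost comparisons with control.
3. The contrast of control with all TXA participants is reported only as a sensitivity analysis.
4. Group 1 versus group 2 continues to use all participants in those groups.

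The cost is a change of wording and a standard error about 4.5% larger for the control contrast (46.1 to 48.2 mL at SD 499). Sample size and the primary analysis do not change.

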### Objectives

The primary objective is to determine if the use of oral TXA post-operatively for up to 24 h will confer a reduction in calculated blood loss at 48 h beyond an intra-operative intravenous bolus alone for patients undergoing unilateral primary THA or TKA.

The secondary objective is to determine if the addition of oral TXA post-operatively to an intra-operative intravenous bolus of TXA produces any change in other measurable parameters compared to those observed for either an intra-operative intravenous bolus alone or no TXA for patients undergoing unilateral primary THA or TKA.

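### For continuous secondary and exploratory outcomes, the only stated contrast with control pools the two TXA groups, which is not the group 1 versus no-TXA comparison in the secondary objective

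*Protocol article*

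**What the plan says.** Under Objectives, the protocol article asks whether adding oral TXA to the intra-operative bolus "produces any change in other measurable parameters compared to those observed for either an intra-operative intravenous bolus alone or no TXA". Read plainly, group 1 has two comparators, group 2 and group 3.

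Under Statistical and interim analysis, the method for the primary outcome and the other continuous outcomes is: "analysis of variance with contrasts will be used to compare both intervention groups", "and also the intervention groups combined versus the control group". For categorical outcomes the text is looser: "The chi-squared test will be used to test the difference in the proportions between the groups for the categorical variables". It does not say which groups are compared or whether any are pooled.

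The Secondary outcome measures section mixes both types. Change in CRP and change in creatinine are continuous. Haemoglobin below the transfusion trigger and the two mortality outcomes are categorical. The body mass index item concerns blood loss.

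**The concern.** This is more than detail left to a later document. The article chooses its contrasts, and the only one that involves control answers a different question from the objective. Groups 1 and 2 combined versus group 3 estimates the average effect of two regimens against none. Group 1 versus group 3 estimates the effect of the full 24-hour regimen against none.

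Pooling suits the interim question, which was whether to go on randomising to group 3. It does not suit a secondary objective about the bolus-plus-oral regimen. An SAP that follows the article would report CRP and creatinine change for TXA in general against no TXA, with no named estimate or test for the regimen under study. If the contrast were added after results had been seen, it would be post hoc.

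**Working it through.** **Inputs from the article.** The SD comes from the sizing statement, "Based on a mean (standard deviation) of 1225 (499) mL of blood loss". The target is "a clinically significant difference of 150 mL (12%) between the two TXA groups", with "233 participants per group at 90% power and 0.05 level of significance" for each joint. Recruitment stood at 672 when group 3 closed, with 134 in group 3. The final target is 466 in each of groups 1 and 2.

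**The plan's own figure.** n = 2 × (1.960 + 1.282)² × 499² / 150² = 232.6, rounded up to 233 per group (two-sided 0.05). The stated size reproduces.

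**What the pooled contrast targets.** Let m1, m2, m3 be the group means.
- Pooled = (m1 + m2)/2 − m3
- Group 1 versus group 3 = m1 − m3 = pooled + ½(m1 − m2)
- Group 2 versus group 3 = m2 − m3 = pooled − ½(m1 − m2)

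The pooled contrast is therefore off by half of the group 1 versus group 2 difference, in opposite directions for the two regimens. At 150 mL that is 75 mL.

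**Two illustrations on the blood-loss scale.** The article gives no SD for CRP or creatinine, so blood loss stands in.
- Bolus alone has no effect, oral adds 150 mL: group 1 versus group 3 is 150 mL, pooled is 75 mL (halved).
- Bolus gives 450 mL, oral adds 150 mL: group 1 versus group 3 is 600 mL, pooled is (600 + 450)/2 = 525 mL, a shortfall of 75/600 = 12.5%. The 450 mL is the interim target for combined TXA; using it for the bolus alone is an assumption.

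**Precision, both joints together.** Participants in groups 1 and 2 at closure: 672 − 134 = 538, or about 269 each under 2:2:1 allocation. Exact arm counts are not given.

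| Contrast | Formula | SE (mL) |
|---|---|---|
| Group 1 v 3, concurrent | 499 × √(1/269 + 1/134) | 52.8 |
| Pooled v 3, concurrent | 499 × √(1/538 + 1/134) | 48.2 |
| Pooled v 3, all participants | 499 × √(1/932 + 1/134) | 46.1 |
| Group 1 v 3, all participants | 499 × √(1/466 + 1/134) | 48.9 |
| Group 1 v 2, all participants | 499 × √(2/466) | 32.7 |

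The concurrent pairwise SE is 52.8/48.2, about 10% above the concurrent pooled SE, and 52.8/46.1, about 14% above the unrestricted pooled SE.

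**Power for a 150 mL effect confined to group 1**, as Φ(effect/SE − 1.96):
- Concurrent participants: pooled (75 mL) 34%, group 1 versus group 3 (150 mL) 81%.
- All participants: pooled 37%, group 1 versus group 3 87%, group 1 versus group 2 99.6%.

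**By joint.** The article plans every analysis for each joint separately as well. The split of the 134 controls is not given; 67 per joint is assumed. With 233 versus 67 the group 1 versus group 3 SE is 69.2 mL and power is 58%. Restricted to concurrent participants, halving both groups gives 52.8 × √2 = 74.6 mL and power of about 52%.

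**The case against.** Much of the case on the other side stands.

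- **Oral-specific effects.** A reader might infer that any effect specific to the oral course is halved. The article does not support that. Group 1 versus group 2 is the comparison that isolates the oral course. It is planned for all continuous outcomes and uses the two largest groups. A creatinine change caused only by oral dosing would appear there at full size. Group 1 versus group 3 mixes bolus and oral effects.
- **Comparison absent everywhere.** A reader might infer that group 1 is never compared with no TXA. That is not shown either. The chi-squared sentence states no pooling, and the Health economic analysis section compares cost per patient in each treatment group. The gap is confirmed only for continuous outcomes, which among the secondary outcomes means CRP and creatinine change.
- **Recoverable estimate.** The group 1 versus group 3 point estimate can be rebuilt as pooled plus half of group 1 versus group 2. This is right, but no such estimate or test is named.
- **Detail for the SAP.** The article says an SAP will be approved before any analysis, and it does not rule out further contrasts. The SAP, which is not shown, may name them. But the article has stated its contrasts, and the one it states against control does not fit its objective.
- **Origin of the pooling.** That it was carried over from the interim analysis is a plausible inference; the article does not say so.

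**Conclusion.** The mismatch is real but limited. For CRP change, creatinine change and the continuous exploratory outcomes, the stated contrast with control does not estimate the comparison in the secondary objective. The discrepancy is half of the group 1 versus group 2 difference. In relative terms it runs from 50%, if the bolus alone has no effect, to 12.5% in the illustration with a 450 mL bolus effect. The primary objective, group 1 versus group 2 on blood loss, is untouched.

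The millilitre and power figures rest on the blood-loss SD of 499 mL as a stand-in, about 269 concurrent participants in each TXA group, and an even split of controls by joint. No size can be given on the CRP or creatinine scale. The algebra holds for any outcome.

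**What to change.** For continuous secondary and exploratory outcomes:

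1. Prespecify group 1 versus group 3 and group 2 versus group 3, beside group 1 versus group 2. Restrict both control contrasts to participants randomised while group 3 was open, so that the groups compared were recruited over the same period under the same 2:2:1 allocation.
2. Keep combined TXA versus control as a supportive contrast.
3. For categorical outcomes, state which groups each chi-squared test compares.

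This is a wording change in the SAP, made before analysis, and needs no further participants or data. The price is two more contrasts per outcome and an SE about 10% wider than the concurrent pooled contrast, or about 14% wider than the unrestricted one. Precision is lower again by joint, so the joint-specific control contrasts are best read as estimates with confidence intervals.
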